### Cognitive Assessments

Participants will be assessed before the TBS sessions and at week 6 with the Psychology Experiment Building Language tests (PEBL) (70) and the E-prime Software (Psychology Software Tools Inc.) (71) using the following tests: Trial Making Test (TMT-A, TMT-B), PEBL computer version (70); Digits test, PEBL computerized version (70); Berg's Wisconsin 64 Card Sorting Test, PEBL computerized version (70); Iowa Test, PEBL computerized version (70); Tower of London Test, PEBL computerized version (70); Cued Emotional Control Test (CECT), E-Prime Software (71); and Internal Shift Task (IST), E-Prime Software (71). Neuropsychological assessment will be applied by trained, blinded neuropsychologists in relation to treatment groups. The assessments will occur at the baseline and at the end of the sixth week after the beginning of the study, with the purpose of evaluating the cognitive performance, with and without emotional valence (cold and hot cognition), for cognitive domains such as: working memory, cognitive flexibility, decision making, processing speed, attention, and inhibitory control (72). An assessment battery of approximately one and a half hours was planned, with the possibility of a 15-min break at half time.

### Reasons for Withdrawal or Termination

Patients will be withdrawn from the study if they meet one or more of the following criteria:

(1) Leave the study on their own accord;

(2) Two consecutive visits OR three or more non-consecutive visits;

(3) Have severe clinical or psychiatric events (at clinical assessment) during the study:.

These criteria will be analyzed on a case-by-case basis according to the clinical assessment that the psychiatrist may be considering. Examples of serious clinical events are: neurological deficits, cardiovascular deficits, endocrine decompensation, loss of consciousness, syncope; and others. Examples of serious psychiatric events are: suicidal ideation, suicide attempt, autoaggressiveness (self-mutilation), hetero-agressivity, severe anxiety, severe psychosis, etc.

(4) Serious adverse effects (at clinical assessment) during the study:

These criteria will be analyzed on a case-by-case basis according to the clinical assessment that the psychiatrist may be considering. Examples of serious adverse effects: severe or frequent headaches, severe cervical pain, severe scalp pain, severe scalp burning, severe dizziness, severe nausea, and seizures.

(5) Worsening of depressive (>25% on the MADRS) or manic (>50% on the YMRS) symptomatology at the end of each week of treatment.

Patients with worsening scores on depressive symptom scales (increase on MADRS scores greater than 25%) or manic symptoms (increase on YMRS scores greater than 50%) at the end of each intervention week (compared to the previous week).

Patients who discontinue the study will be referred to the psychiatrist who referred the study for appropriate follow-up and management of the disease.

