Clinical assessments will be conducted weekly until the end of week 3 and thereafter a final assessment will be conducted at the end of week 6. Adverse events will be evaluated every day during the first week and then once a week until the end of the week 6. The neuropsychological assessment battery will be applied before the patient is stimulated and at the end of the week 6 of intervention (**Table 2**).

**Table 2 T2:** Measurement outcomes over time.

Scales	Baseline	End of week 1	End of week 2	End of week 3	End of week 6
SCID I/P modified	X				
MADRS	X	X	X	X	X
YMRS	X	X	X	X	X
*WHOQOL-bref*	X	X	X	X	X
BIS-11	X	X	X	X	X
CGI-S	X	X	X	X	X
GAF	X	X	X	X	X
HAM-A	X	X	X	X	X
BRIAN	X	X	X	X	X
Morningness–Eveningness Questionnaire	X				
TMS' Typical side Effects Scale	X	X	X	X	X
UKU-SERS	X	X	X	X	X
Neuropsychological Assessment	X				X

SCID, Structured Clinical Interview; MADRS, Montgomery–Åsberg Depression Scale; YMRS, Young Mania Rating Scale; WHOQOL, World Health Organization questionnaire; BIS-11, Barratt Impulsivity Scale; GAF, Global Assessment of Functioning; HAM-A, Hamilton Anxiety Scale; BRIAN, Biological Rhythm Interview of Assessment in Neuropsychiatry; TMS, transcranial magnetic stimulation; UKU-SERS, Udvalg for Kliniske Undersøgelser Side Effect Rating Scale; CGI-S, Clinical global impression - Severity.

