### Intervention

TBS sessions will be performed using MagPro X100 TMS device (Magventure, Lucernemarken, Denmark) and Cool-B65 A/P (Magventure, Lucernemarken, Denmark) coil. An identical butterfly coil for both active and sham stimulation will be used. The coil will be positioned over the DLPFC and the cortical location will be obtained through anatomical measurements (F3 and F4 positions determined by the 10–20 Electroencephalographic International System) on the right and left. As most mixed depressive episodes are resistant to drug treatment and there are no clinical trials evaluating TBS specifically in mixed depressive episodes so far, we replied a study protocol (41) that evaluated TBS in resistant major depressive episodes of MDD. The bilateral TBS sections will be applied in the following order: first inhibitory stimulation—cTBS—in the right DLPFC followed by excitatory stimulation—iTBS—in the left DLPFC with the following parameters: in cTBS bursts of three pulses at 50 Hz (20-ms interval between stimuli) will be applied continuously for 120 s totaling 1800 pulses in the right DLPFC and iTBS bursts of three pulses at 50 Hz (20-ms interval between stimuli) will be applied for 2-s duration repeated every 10 s for a total time of 570 s also totaling 1800 pulses in the left DLPFC, both with 80% of visual motor threshold (64). We will use a magnetic stimulator device (MagVenture^©^, United States) in study mode for double-blind trials. Participants will perform one session a day over five consecutive days (Monday to Friday) at the first, second and third weeks and then sessions 2 days a week, with an interval of at least 1 day between sessions, for a further 3 weeks of active or sham TBS.

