### Sample Size Calculation

There are no studies on mixed depression using neuromodulation techniques, so that we used a study that used a similar methodology (bilateral TBS) (41) for treatment-resistant unipolar depression that found a reduction of 52.5% of the depression scale for the active group and a reduction of 17.4% of the depression scale for sham group (F/X^2^ = 6.166). The sample size calculation took into account this measure of effect size obtained in the study cited and was performed with Stata^®^ Statistical Software. The total number of participants we calculated was 82 participants, taking into account 90% power and 5% alpha. As this is a long term study we estimate a dropout rate of 10%, similar to recent studies in this field (37). Thus, we will need to recruit 90 patients, 45 participants in each group (active versus sham).

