## Discussion

Here we provided the study protocol of a randomized controlled trial (RCT) that will evaluate the efficacy of TBS for the treatment of mixed depression of both bipolar and unipolar disorders. To the best of our knowledge, this is the first study in this field. Will be applied 21 sessions of bilateral TBS, comprising first inhibitory stimulation delivered by cTBS in the right DLPFC followed by excitatory stimulation delivered by iTBS in the left DLPFC, totalizing 3600 pulses. We performed sample size calculation based on the effect size found in the most similar clinical trial found in literature (41). The CANMAT guidelines provide the first- and second-line adequate treatments to treat both unipolar and bipolar depression (55). So far, there is no scientific recommendations to treat mixed depression. So that, we will include patients in a regular use (at least 30 days) of a first or second-line treatment of a CANMAT treatment and still presents with a moderate or severe major depressive episode. Patients with different drug treatments will be included, which will significantly increase the external validity of the results (73).

Previous studies indicate that mixed features population have distinct clinical and treatment response characteristics and has been associated with higher comorbidities, higher relapse rates, worse clinical outcomes, and higher suicide risk (51, 74, 75). We defined the MADRS (48) to assess depression symptoms and YMRS (49) to assess maniac symptoms. While some studies defined mixed depression considering YMRS ≥ 4 points (51, 74), recent data suggests that YMRS with ≥ 1 point on three or more items according are appropriate to classify this issue (12). Although any RCT with TBS has been performed so far in mixed depression, one clinical trial evaluated the efficacy of bilateral TBS in refractory non-mixed depression (41). Our RCT differs from this one in several ways, including a larger sample size (90 vs. 60) and comprising mixed depression presentation of both BD and MDD. In addition to the primary outcome that will assess the efficacy of TBS in mixed depression, this study will evaluate the effect of this technique on anxious symptoms, impulsivity, biological rhythms, functionality, quality of life, and cognition, the latter through a computerized neuropsychological battery.

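### Withdrawal criterion 2 ends study participation for non-attendance in an undefined unit; name the unit and keep rating these patients, above all at week 3

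*Protocol article*

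**What the plan says.** Under Reasons for Withdrawal or Termination, the list opens with "Patients will be withdrawn from the study if they meet one or more of the following criteria". Criterion 2 reads in full "Two consecutive visits OR three or more non-consecutive visits". The section closes by referring patients who discontinue back to their psychiatrist; it mentions no later rating.

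Elsewhere the article counts in two other units:

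- **Sessions.** Intervention: "Participants will perform one session a day over five consecutive days (Monday to Friday) at the first, second and third weeks", followed by two a week for three weeks. Discussion: "Will be applied 21 sessions of bilateral TBS".
- **Ratings.** Inclusion and Exclusion Criteria: "Clinical assessments will be conducted weekly until the end of week 3 and thereafter a final assessment will be conducted". Table 2 agrees, with MADRS and YMRS at baseline and at the end of weeks 1, 2, 3 and 6.

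The primary outcome is the MADRS change from baseline to week 3 (Measurement of Variables and Outcomes). On attrition, Sample Size Calculation says "we estimate a dropout rate of 10%, similar to recent studies in this field", which takes 82 participants to 90.

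**The concern.** Taken literally, criterion 2 does not say what the patient must have done with the visits. Once missed is supplied, the unit is still open. Site staff counting sessions and site staff counting ratings would apply very different rules, and the article uses the word visits nowhere else that could settle it.

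The consequence matters more than the wording. Withdrawal is from the study, so a patient who stops attending stimulation is also lost to the ratings still to come, including week 3 if the criterion is met before then. Those ratings are already on the schedule. If non-attendance is related to mood or tolerability, which is plausible but not shown in the article, the loss is not random and can bias the comparison as well as shrink it.

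**Working it through.** **The plan's own figure.** 82 / 0.90 = 91.1 and 82 × 1.10 = 90.2. The stated 90 lies within two patients of either rounded-up result (92 or 91). The actual margin is 90 − 82 = 8 patients, or 8/90 = 8.9%.

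**Which unit gives both clauses a meaning?** Among four ratings in sequence, at most two can be missed without two being adjacent. Three misses therefore always meet the first clause, and the second is redundant. Among 15 or 21 sessions, three scattered misses are possible, so both clauses do something. This favours sessions, but the text does not say so.

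**Share withdrawn.** Let n be the number of scheduled contacts, p the chance of missing each one, and q = 1 − p. Assume that misses are independent and that a Friday and the next Monday count as consecutive. A patient escapes the criterion with no miss, one miss, or two non-adjacent misses, and there are C(n−1, 2) ways to place two non-adjacent misses. So

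P(withdrawn) = 1 − [qⁿ + n·p·qⁿ⁻¹ + C(n−1, 2)·p²·qⁿ⁻²].

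With p = 5%:

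- Week 3, n = 15: 1 − (0.4633 + 0.3658 + 0.1168) = 0.054, or 4.9 of 90.
- Week 6, n = 21: 1 − (0.3406 + 0.3764 + 0.1792) = 0.104, or 9.3 of 90.

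The miss rate is my assumption, so here is the range:

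| Miss rate | By week 3 (15 sessions) | By week 6 (21 sessions) | Read as 4 ratings |
|---|---|---|---|
| 3% | 1.8% | 3.4% | 0.3% |
| 5% | 5.4% | 10.4% | 0.7% |
| 7% | 11.0% | 20.3% | 1.4% |
| 10% | 22.0% | 37.9% | 2.8% |

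**Where the allowance is reached.** Setting P = 10% gives p = 6.7% for 15 sessions, 4.9% for 21 sessions, and about 20% for four ratings. Setting P = 8/90 gives 6.3% for 15 sessions and 4.6% for 21.

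**If patients differ in their miss rate.** With beta-distributed rates (intraclass correlation 0.05 to 0.2), the week-6 share is about 8% to 9% at a mean of 3% and 15% to 16% at 5%, above the independent figures. At a mean of 10% it is 30% to 36%, slightly below 37.9%. Heterogeneity therefore worsens the picture only at the lower rates.

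**Power at week 3.** Take the stated 90% power at 82 participants as given. Two-sided 5% and 41 per arm imply a standardised difference of (1.960 + 1.282) × √(2/41) = 0.716. Power with m per arm is Φ(0.716·√(m/2) − 1.960). If criterion 2 were the only source of loss and every such patient contributed nothing:

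- p = 3%: m = 44.2, power 92%
- p = 5%: m = 42.6, power 91%
- p = 10%: m = 35.1, power 85%

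**The case against.** A reader might infer that the criterion deletes outcomes. The article does not support that. It discards no rating already taken, Statistical Analysis keeps patients who withdrew under the protocol in the per-protocol set, and a linear mixed model can use their week-1 and week-2 scores. What is lost is later data. At a 5% miss rate about half of the withdrawals (9.3 − 4.9 ≈ 4.5 of 9.3 patients, from unrounded figures) come after the week-3 rating and cost only week-6 data.

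A reader might also infer that the criterion by itself exhausts the 10% allowance. At 5% that is true only over all 21 sessions. By the primary endpoint the figure is 5.4%, inside the allowance. No miss rate is documented, and the 10%, taken from studies that the article cites, may already include non-attendance.

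Nor should one picture many patients with 13 of 15 sessions and no week-3 score. If withdrawal follows the trigger at once, that happens only when the two missed sessions are the last two of week 3.

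Finally, the missing word is plainly a slip, the second clause points to sessions, and an article may leave a definition of visit to the full protocol. I accept this: the undefined unit alone would be a small clarification. What stands is that the article does state the consequence, withdrawal from the study followed only by referral. Followed as written, that forgoes ratings that are already planned.

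**Conclusion.** The point holds as a cheap improvement, not as an error that breaks the design. Criterion 2 needs its unit named, because at a 5% miss rate the two readings differ about 14-fold (10.4% against 0.7%). Read as sessions, it takes 1.8% to 22% of patients out before the primary endpoint, and 3.4% to 38% by week 6, over assumed miss rates of 3% to 10%. The effect on power at week 3 is negligible at 3% to 5% and noticeable near 10%. The stronger reason to act is possible bias from patients who stop attending and are then not rated, which the article gives no means of sizing. All shares rest on assumed miss rates, and the table on independent misses as well; the power figures also take the article's 82 as given.

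**What to change.** 1. In criterion 2, state that missed visits are meant and name the unit, so that Reasons for Withdrawal or Termination, Intervention and the assessment schedule agree.
2. Whatever stopping rule for stimulation the sponsor keeps, state that meeting it does not end follow-up. Patients who agree are still rated on MADRS and YMRS at the remaining scheduled assessments, in particular week 3.
3. State that these ratings are used at least in the ITT analysis. That set, as defined, requires one week of treatment, so say how a patient who meets the criterion during week 1 is handled. Read as sessions, this is about 1% of patients at a 5% miss rate and 3.8% at 10% (n = 5 in the formula above).

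The cost is a wording amendment and the effort of contacting some non-attenders for up to four ratings already on the schedule. No clinical stopping rule is proposed here.

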**Methods:**

The study is designed as a randomized, sham-controlled, double-blinded clinical trial evaluating TBS for the treatment of moderate or severe major depressive episodes with mixed features of patients receiving at least one first or second-line pharmacological treatment for depressive episodes without adequate response. Ninety adult (18 to 65 years old) patients will be enrolled and submitted to 6-week (comprising 5 consecutive days a week sessions for the first 3 weeks and then 2 days a week for a further 3 week) of inhibitory followed by excitatory TBS in dorsolateral prefrontal cortex. Participants will be assessed using clinical and neuropsychological tests before and after the intervention. The primary outcome is change in Montgomery–Åsberg Depression Scale (MADRS) score over time and across groups. Cognitive parameters will also be assessed with neuropsychological tests.

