Primary outcome will be change in MADRS from baseline to week 3. Secondary outcomes will be: change in YMRS at the end of week 3 and 6 of treatment; response rates (50% or more of reduction in MADRS at the end of weeks 3 and 6 of treatment); remission rates (MADRS <11 (56) at the end of weeks 3 and 6 of treatment); change in anxious symptoms assessed by Hamilton Anxiety Scale (HAM-A) (57) at the end of weeks 3 and 6 of treatment; change in overall clinical impression assessed by Global Clinical Impression of Severity (GCI-S) (58) and Global Assessment of Functioning (GAF) (59) at the end of weeks 3 and 6 of treatment; change of functionality assessed by abbreviated version of the World Health Organization questionnaire (WHOQOL) (60) at the end of weeks 3 and 6 of treatment; change of biological rhythms assessed by the Biological Rhythm Interview of Assessment in Neuropsychiatry (BRIAN) (61) at the end of weeks 3 and 6 of treatment; change of impulsivity assessed by Barratt Impulsivity Scale (BIS-11) (62) at the end of weeks 3 and 6 of treatment; association between the chronotype assessed by Morningness–Eveningness Questionnaire (63) and the severity of mixed depression assessed by MADRS; and change in neuropsychological battery parameters before and at the end of the intervention (6 weeks).

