### Statistical Analysis

Statistical analyses will be performed using Stata^®^ (67) and the Statistical Package for the Social Sciences—SPSS^®^ (68). The overall significance level for this study will be 0.05 using two-tailed tests. The study results will be analyzed for two patient populations: the intention-to-treat (ITT(and the per-protocol (PP) analysis set. The ITT set will include all subjects who met the study eligibility criteria and received at least one week active/sham TBS treatment. The PP population thus will include all subjects from the ITT set who receive the protocol-specified treatment and complete the 6-week treatment regimen or withdrew before completion per the study protocol. Comparisons of baseline demographic and clinical characteristics and safety assessments will be performed on the ITT analysis set. The primary efficacy analysis will be performed using the PP analysis set.

Comparisons of baseline demographic and clinical characteristics between the study groups will be performed to ensure that the groups are balanced at baseline and that the randomization is successful. For comparison of means (continuous variables), the two-sample t-test or a nonparametric equivalent will be used. For comparison of proportions (categorical variables), the chi-square test or Fisher's exact test will be used, as appropriate. The change in MADRS total score from baseline to week 3 (primary endpoint) will be compared between the treatment groups using a linear mixed model (69) with a continuous dependent variable (MADRS score) to measure the primary outcome. For primary outcome subject will be the random effect and the fixed factors will be intervention (sham × active). Secondary outcomes will also follow the same pattern and the scales' scores will be the random effect and the fixed factors will be intervention (sham × active). Since patients will be taking different medications and dosages, the defined daily dose (DDD) will be used in the statistical analysis. This enables the inclusion of several medications and doses in the model, as medication groups (e.g., antidepressants, anticonvulsants, etc.).

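### The worsening rule ends study participation, not only stimulation, so week-3 primary and week-6 scores are lost that continued rating at visits already scheduled could keep

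*Protocol article*

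**What the plan says.** The list in Reasons for Withdrawal or Termination opens with "Patients will be withdrawn from the study if they meet one or more of the following criteria". Criterion 5 is "Worsening of depressive (>25% on the MADRS) or manic (>50% on the YMRS) symptomatology at the end of each week of treatment", and the explanatory text fixes the comparison as "at the end of each intervention week (compared to the previous week". The section ends: "Patients who discontinue the study will be referred to the psychiatrist who referred the study for appropriate follow-up". The article does not separate stopping stimulation from leaving the study.

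On timing, the schedule (text before Table 2) reads "Clinical assessments will be conducted weekly until the end of week 3 and thereafter a final assessment will be conducted"; Table 2 places that last rating in week 6. Measurement of Variables and Outcomes states: "Primary outcome will be change in MADRS from baseline to week 3". Response, remission and the other clinical scales are secondary outcomes at weeks 3 and 6.

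Statistical Analysis puts the primary efficacy analysis on the per-protocol set, which takes in patients who "complete the 6-week treatment regimen or withdrew before completion per the study protocol". Read literally, a patient stopped under criterion 5 stays in that set.

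**The concern.** The loss is triggered by the outcome scale itself (MADRS) or by a key secondary scale (YMRS), and scores never collected cannot be added later. A patient stopped at week 1 or 2 can sit in the primary analysis set without the score that defines the primary endpoint.

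The rule can also fire on a small change. Mixed features need only 1 point on each of three YMRS items, so a YMRS total of 3 is possible at entry, and 3 to 5 is a rise of 2/3 = 67%. Because the reference is the previous week and not baseline, a patient who has improved greatly can be withdrawn: MADRS 10 to 13 is a rise of 3/10 = 30%. The later scores of such a patient are clearly of interest.

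At stake are the completeness of the primary endpoint and of the week-6 outcomes, and some power.

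**Working it through.** **1. What each trigger loses.** Ratings are at baseline and weeks 1, 2, 3 and 6.

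| Trigger at end of | Week-3 MADRS | Week-6 outcomes |
|---|---|---|
| Week 1 or 2 | lost | lost |
| Week 3 | kept | lost |

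No clinical rating falls in weeks 4 and 5, so the rule cannot act then on the stated schedule.

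**2. The plan's own figures.** The article states 82 evaluable patients for 90% power at two-sided 5%, 10% dropout, and 90 recruited. Check: 82 × 1.1 = 90.2 and 82 / 0.9 = 91.1, so 90 is reproduced within 2 patients. Also 90 × 0.9 = 81. The 82 cannot be rebuilt from the documents, because no standard deviation is given. Working backward with a two-sample t-test, 41 per arm and 90% power imply a standardised difference of 0.725.

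**3. How often the rule fires (assumptions, not document figures).** The grid has mean YMRS 4, 6, 8, 10; YMRS error SD 0.7, 1.0, 1.5; MADRS error SD 2, 3; MADRS slope SD 4, 8. That is 4 × 3 × 2 × 2 = 48 scenarios, with 200,000 simulated patients per arm before entry limits (MADRS at least 20, YMRS at least 3).

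Held fixed:
- Baseline MADRS 29 (SD 5), with linear improvement by week 3 of 8 on sham and 14.5 on active.
- YMRS SD 2, improvement 1 on sham and 2 on active, slope SD 1; slope correlation 0.5.
- Scores are rounded and compared with the previous observed week.

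Week-3 scores lost, both arms combined (%; each cell gives the range over the MADRS settings):

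| YMRS error SD | Mean YMRS 10 | 8 | 6 | 4 |
|---|---|---|---|---|
| 0.7 | 0.4–4.8 | 0.9–5.2 | 2.2–6.4 | 4.4–8.5 |
| 1.0 | 1.2–5.5 | 3.1–7.2 | 6.6–10.7 | 10.8–14.6 |
| 1.5 | 5.9–9.9 | 10.9–14.7 | 17.1–20.7 | 22.2–25.4 |

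The median is 6.9% (90 × 0.069 = 6.2 patients) and the maximum 25.4% (90 × 0.254 = 22.9). In 31 of 48 scenarios the loss is at or below 10%. A further 0.5% to 16.3% first trigger at week 3 and lose week 6 only.

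A second set of assumptions takes the percentage reductions quoted in Sample Size Calculation (52.5% active, 17.4% sham) as the mean falls, with baseline MADRS 30, MADRS error SD 2 to 4, YMRS 6 to 10 and YMRS error SD 1 to 2. It gives more: 9–20% lost on active and 14–32% on sham.

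**4. Bias on the week-3 difference.** In the grid the true difference is 6.2 to 6.5 points. An analysis of completers only falls short by 0.02 to 0.40 points, toward zero. A likelihood analysis using all weekly scores, with time by arm, is within 0.03. With the same improvement assumed in both arms, losses were equal within 0.1 percentage point (23.5% vs 23.5%; 28.6% vs 28.5%).

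**5. Power at d = 0.725**, counting each week-1 or week-2 stop as a full loss on top of 10% other dropout:

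| Case | N with a week-3 score | Power |
|---|---|---|
| No criterion-5 loss | 81 | 89.7% |
| Median | 81 × (1 − 0.069) = 75.4 | 87.4% |
| Worst case | 81 × (1 − 0.254) = 60.4 | 79.1% |

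The differences are 89.7 − 87.4 = 2.3 points and 89.7 − 79.1 = 10.6 points. Both are upper bounds, for the reasons given under the objection.

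**The case against.** The strongest reply is that nothing planned is invalid, and that stands. Withdrawal under criterion 5 depends on observed scores, so a mixed model using all weekly scores handles it well. The abstract describes the outcome as MADRS "score over time and across groups", which points that way. Statistical Analysis names only intervention as a fixed factor, so the use of time should be confirmed, but a condensed article is not evidence that time is left out.

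Second, scores after the stop answer a different question. Stimulation has ended and the referring psychiatrist may change drugs, whereas the trial studies TBS on a fixed regimen. Putting those scores into the primary per-protocol analysis would move it toward a treatment-policy question. This stands as to how the scores are used. It does not count against collecting them, because scores up to the stop still serve the on-treatment analysis.

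Third, the power gain is overstated if read as a forecast. Recovered scores are credited with the full effect, which patients off stimulation may not show. The stated 10% dropout does not exclude protocol-mandated stops; if they fall within it, the median scenario costs no planned power. A mixed model would also recover part of the loss. All of this stands. The grid median is a summary of chosen scenarios, not an expected value.

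Fourth, the full protocol might continue ratings. That is possible, but the article does more than stay silent: it states withdrawal from the study.

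A reader might infer that the rule invites a false-positive result or makes the primary analysis invalid. Neither is supported: the bias is toward zero, and with no treatment effect the losses are balanced. Nor do the documents show that losses will exceed the dropout allowance. That depends on assumed YMRS levels and error.

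**Conclusion.** The point holds as a cheap improvement of minor to moderate priority. It is not an error in the planned analysis. What is certain from the text is that criterion 5 ends participation, that a trigger at week 1 or 2 loses the week-3 MADRS, and that every trigger loses the week-6 outcomes. How much is lost is uncertain: roughly 0.4% to 25% of week-3 scores in the 48-scenario grid. Losses above 15% arise there only with YMRS error SD 1.5 and mean YMRS of 6 or less, though the second set of assumptions gives higher losses. Bias is at most 0.40 points on about 6, toward zero, and close to nil if all weekly scores are modelled over time. The power at stake is at most about 2 points at the median and 10 in the worst case.

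**What to change.** Leave the thresholds, the safety stop and the referral as they are, and change what follows:

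- Criterion 5 stops stimulation. MADRS and YMRS ratings continue at the remaining Table 2 visits (weeks 2, 3 and 6, as applicable) unless the patient withdraws consent.
- Record medication and other treatment changes after the stop.
- Report criterion-5 stops by arm and by week.
- Use the post-stop scores in an intention-to-treat (treatment-policy) analysis by randomised arm, and describe that effect as including changed care.
- Keep the planned primary analysis on scores up to the stop, unless the sponsor decides to change what it estimates. Confirm that its mixed model uses all weekly scores over time.

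Cost: a small amendment and no new visit type. At the grid median there are at most 6.2 × 3 = about 19 extra rating visits. In the worst case there are at most 23 × 3 + 90 × 0.163 = 69 + 15 = 84, the second term being week-6 ratings after week-3 stops. These visits fall on patients who have just worsened, which is a real burden. The article says recruitment was not complete at submission. If enrolment is under way, patients before and after the amendment will have different follow-up, and the report should say so.
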